## 2. Methods and Analysis

### 2.1. Design

EARLY PRO-TECT Alport is a phase III, multicenter, randomized, placebo-controlled, double-blind (patient, investigator and trial team http://www.clinicaltrials.gov/) clinical trial conducted in Germany according to the German Medicines Act (Arzneimittelgesetz). Up to 80 previously untreated AS patients with Alport stages 0 or I at screening (Table 1) will be randomized into once-daily treatment over 3 years with ramipril or placebo. Patients will be randomized (stratified by trial site) at a 1 : 1 ratio using permutated blocks (Figure 1). Upon disease progression (Table 2) during the treatment period, patients are unblinded, and ramipril treatment is initiated, if applicable. Approximately 40 AS patients will be treated open label with ramipril and will contribute to the safety database. This group includes previously treated as well as untreated patients who or whose parents/legal guardian refuses randomization because they request treatment.

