### 2.4. Sample Size

The sample size/power calculation is driven by the primary efficacy endpoint, that is, the time to progression of Alport syndrome to the “next disease level” (Table 2). The proportions of patients who remain in one disease level during the study period of 3 years were estimated to be approximately 50% on placebo and approximately 80% on ramipril; that is, 50% of patients on placebo and 20% of patients on ramipril are expected to progress in disease level. This corresponds to a hazard ratio of 0.322. With a two-sided test at *α* level of 0.05, equal allocation to both groups, and an assumed hazard ratio of 0.322, the numbers of events of “next disease level” required to achieve a power of 80% and 90% are 24 and 33 [10], respectively. A sample size of 80 patients will provide 28 events within a fixed 3-year observation period (intervention time) and will therefore give a power in excess of 80%. Dropouts are unlikely in this population, because older relatives in these families are often severely affected—increasing the high degree of compliance towards a potentially renal-protective therapy in patients and parents.

The total time on ramipril is expected to be about 270 person-years with the patients randomized to ramipril contributing by 120 person-years (40 patients for 3 years), the open-label use by another 120 person-years (40 patients for 3 years), and the patients randomized to placebo who receive ramipril upon disease progression contributing by 30 person-years (estimated 20 patients with disease progression after an average of 1.5 years). Assuming a Poisson distribution of the events, this total length of followup is sufficient to estimate an adverse event rate of 1 in 10 person-years with a precision of 20%.

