### 2.7. Statistical Analysis

The primary efficacy endpoint “time to progression to the next disease level” for randomized patients will be assessed in 6-monthly intervals over the treatment period of 3 years. A proportional hazards' model for interval-censored data will be applied with effects for treatment, trial site, and proteinuria at start of therapy. If indicated, additional potentially confounding variables such as genotype and age will be added to the model. An estimate of the treatment effect is reported in terms of the hazard ratio with 95% confidence interval and *P* value testing the null hypothesis of no effect.

The primary safety endpoint is the “incidence of adverse drug events (ADE), for example, angioedema, acute renal failure, hyperkalemia, under ramipril treatment before disease progression compared to placebo before disease progression, for all randomized patients.” The incidence rates will be analyzed using a generalized linear model with log link (Poisson regression) and corrected, if necessary, for overdispersion due to interpatient heterogeneity. An estimate of the treatment effect is reported in terms of the rate ratio with 95% confidence interval and *P* value testing the null hypothesis of no effect.

The secondary efficacy endpoint “albuminuria after 3 years corrected for baseline albuminuria for patients randomized to receive ramipril compared to placebo” will be analyzed by means of an analysis of covariance (ANCOVA) with treatment, trial site, and proteinuria at start of therapy as factors and baseline albuminuria as covariate. The treatment effect estimate in terms of a mean difference will be reported with 95% confidence interval and *P* value testing the null hypothesis of no treatment effect. The *secondary safety endpoint* “incidence of ADEs during 3 years of treatment for patients randomized to receive ramipril compared to placebo” will be carried out in the same way as the primary safety analyses described above. Other secondary end points include eye involvement and hearing loss. Results will also be stratified by age groups. No interim analyses are planned.

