**Figure 2 fig2:**
[figure not shown]
Study visits for the individual patient during the EARLY PRO-TECT Alport.

**Table 1 tab1:** Alport syndrome levels describing renal damage and loss of function.

Stage	Definition
0	Microhaematuria without microalbuminuria (usually at birth)
I	Microalbuminuria (30–300 mg albumin/gCrea)
II	Proteinuria >300 mg albumin/gCrea
III	>25% decline of normal renal function (creatinine clearance)
IV	End-stage renal failure (ESRF)

**Table 2 tab2:** Alport syndrome disease progression in this trial.

Progression	Definition
Stage 0 to I	Albuminuria >30 mg albumin/gCrea in combination with a 3-fold increase from baseline in albuminuria, confirmed within 2 weeks.
Stage I to II	(i) Twofold increase from baseline albuminuria, confirmed within 2 weeks
	(ii) Albuminuria >300 mg albumin/gCrea at a single assessment.

**Table 3 tab3:** Patient eligibility criteria.

	*Inclusion criteria*
	(i) Males or females of any ethnic origin aged between 24 months and <18 years at screening. Female patients of child-bearing potential test negative for pregnancy test and agree to use a reliable method of birth control during the study.
	(ii) Definitive diagnosis of Alport syndrome by kidney biopsy (in patient or other affected family members) and/or genetic testing (hemizygous males with X chromosomal Alport syndrome or homozygous males or females with autosomal recessive Alport syndrome) including screening for clinical diagnostic criteria (hematuria, family history of kidney disease, hearing loss, ocular changes).
	(iii) Alport syndrome stages 0 or I.
	(iv) Previously untreated with ACEIs (patients taking an ACEI for the treatment of Alport syndrome may be included in the open-label treatment arm).
	(v) Written informed consent.

	*Exclusion criteria*
	(i) Uncertain diagnosis or variants of Alport syndrome such as heterozygous carriers.
	(ii) Alport syndrome stages II, III, or IV.
	(iii) Known allergies or intolerances to ramipril or related compounds.
	(iv) Known contraindication for ACEI therapy (e.g., bilateral renal artery stenosis, prior history of angioedema, previous hyperkalemia, or previous acute prerenal renal failure).
	(v) Females with a positive pregnancy test or females who are lactating.
	(vi) Additional other chronic renal, liver, or cardiac diseases.
	(vii) No written informed consent.

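### The 3-year albuminuria ANCOVA by randomised arm estimates early versus deferred ramipril; read as ramipril versus placebo, it is attenuated towards no difference

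*Protocol article*

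**What the plan says.** Section 2.7 sets the endpoint as "albuminuria after 3 years corrected for baseline albuminuria for patients randomized to receive ramipril compared to placebo". It is analysed by ANCOVA, adjusted for site, for initial proteinuria and for the baseline value of the outcome. The planned report reads: "The treatment effect estimate in terms of a mean difference will be reported with 95% confidence interval". A P value accompanies it. The text does not limit the endpoint to time before progression and does not say how values after a switch are treated.

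Four other places bear on this:

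- Section 2.1: "Upon disease progression (Table 2) during the treatment period, patients are unblinded, and ramipril treatment is initiated, if applicable".
- Section 2.4: "50% of patients on placebo and 20% of patients on ramipril are expected to progress in disease level". The ramipril exposure count in the same section includes 30 person-years from placebo patients who switch, described as "estimated 20 patients with disease progression after an average of 1.5 years".
- Table 2: progression is defined entirely by albuminuria. For stage I to II, one criterion is "Twofold increase from baseline albuminuria, confirmed within 2 weeks".
- Section 2.7, primary safety endpoint: this one is restricted to the period before progression in both arms. The 3-year comparison of adverse drug events by randomised arm is kept as a separate, secondary endpoint.

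**The concern.** By the time the 3-year sample is taken, a large part of the placebo arm is expected to be taking the study drug. These patients are not a random subset: they switch because their albuminuria rose. The Background section cites evidence that ACE inhibitors reduce proteinuria, so their 3-year values should on average be lower than if they had stayed on placebo. The ramipril arm has no matching change, since its progressors are already on the drug. The attenuation therefore runs in one direction, towards no difference.

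The trial is meant to support a treatment recommendation and a marketing authorisation. A small 3-year difference reported as the effect of ramipril against placebo could be taken to mean that ramipril does little for albuminuria, when part of the explanation is that both arms were by then being treated.

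**Working it through.** **1. The plan's own figures.** Inputs are from section 2.4: 3-year progression 50% on placebo and 20% on ramipril, 40 patients per arm, and "With a two-sided test at *α* level of 0.05".

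- Hazard ratio = ln(0.8)/ln(0.5) = 0.3219 (stated 0.322).
- Events needed (Schoenfeld) = 4(1.960 + z)²/(ln 0.322)² = 24.4 for 80% power and 32.7 for 90% (stated 24 and 33).
- Events expected = 40 × 0.5 + 40 × 0.2 = 28, which gives 85% power (stated as above 80%).
- Placebo switchers = 40 × 0.5 = 20. Their ramipril time = 20 × 1.5 = 30 person-years, and the total is 120 + 120 + 30 = 270 (as stated).

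The figures reproduce. A switch by half the placebo arm is the plan's own expectation.

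**2. Share of the placebo arm on ramipril at the 3-year sample (s).** The upper value is s = 0.50. Visits are 6-monthly, and a patient first found to progress at month 36 has not yet been treated. Under a constant hazard with 50% progression at 3 years, the share found by month 30 is 1 − 0.5^(2.5/3) = 0.44.

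**3. Simple dilution.** Let r be the share of the full ramipril effect that a switcher has reached by month 36. The article does not give r, so it is varied. Retained effect = 1 − s × r. The article gives no power for albuminuria, so the benchmark is an assumed comparison with 80% power without switching. Then power = Φ(2.802 × retained − 1.960), and n per arm must grow by 1/retained² to restore it.

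| s | r | Retained | Power | Factor on n |
|---|---|---|---|---|
| 0.50 | 1 | 50% | 29% | 4.0 |
| 0.50 | 0.75 | 62.5% | 42% | 2.6 |
| 0.50 | 0.5 | 75% | 56% | 1.8 |
| 0.50 | 0.25 | 87.5% | 69% | 1.3 |
| 0.44 | 1 | 56% | 35% | 3.2 |

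**4. Switching triggered by albuminuria.** The formula above treats switchers as average patients. A simulation instead let a twofold rise at a 6-monthly visit trigger the switch. Assumptions:

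- yearly log slopes normal with mean ln(2)/3 and SD 0.15 to 0.35, which gives 50% placebo progression;
- ramipril acting as an immediate drop of 0.3 or 0.5 log units, as a halving or stopping of the slope, or as a drop of 0.3 with a halved slope.

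The share of placebo patients treated before month 36 was 38–45%. The log-scale difference retained was 55–81%. The scenario with ramipril-arm progression closest to the planned 20% (17.8%) retained 68%. A second check with about 42% placebo progression retained roughly 67–92%.

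For a true geometric mean ratio of 0.60, a further check with a confirmed twofold trigger gave two cases. A gradual slope effect retained about 80% (power 83% falling to 70%). An immediate effect reached over 10 months retained about 62% (power 83% falling to 52%).

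On the untransformed scale, the first simulation retained 18–71%. That figure also reflects the skewness of albuminuria, a separate matter, and the article does not state the analysis scale. It is not used for the conclusion.

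**5. Does the alternative work?** A likelihood-based repeated-measures analysis used values up to and including the progression-defining sample. In the trigger-based scenario with 47% placebo and 17% ramipril progression, it gave −0.497 against a true log difference of −0.498. Across that set of scenarios it was within about 6% of the truth. The as-randomised 3-year contrast in the same scenario kept 58% of the effect if the post-switch effect is full, and 79% if it is half.

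**The case against.** The strongest reply is that the endpoint is worded by randomisation. A comparison by assigned arm is a legitimate treatment-policy question, and for that question the ANCOVA is not biased. The secondary safety endpoint uses the same as-randomised 3-year form, so the choice may be deliberate. This stands: the analysis should be kept. What it leaves open is the interpretation, because the deferred ramipril in the control arm is nowhere acknowledged as part of the contrast.

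A reader might infer that the trial has no measure of albuminuria before the switch. That is not so. Table 2 makes the primary endpoint an albuminuria measure that ends at progression, and the switch does not touch it. For the same reason, a smaller 3-year difference after deferred treatment would not in itself contradict a positive primary result. Nor is albuminuria the only secondary efficacy outcome, as section 2.7 also names eye involvement and hearing loss.

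A reader might also infer that the effect is halved and most of the power lost. That requires all 20 progressors to be treated and at full effect by month 36. Section 2.1 starts ramipril only if applicable, progressors found at month 36 are untreated at that sample, and section 2.3 describes uptitration over 10 months for previously untreated patients.

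Finally, the handling of post-switch values could sit in a full protocol or analysis plan that is not shown, so its absence from the article is no fault. The point rests on what the article does fix: endpoint, time point, contrast and model.

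**Conclusion.** The point holds with a limited claim. By the plan's own figures, up to 20 of 40 placebo patients (about 44% of the arm, leaving out those first found to progress at month 36) will have started ramipril before the 3-year value is taken. The planned ANCOVA is a valid comparison of early with deferred ramipril. As an estimate of ramipril against placebo it is attenuated, and that direction is clear provided ramipril lowers albuminuria in switchers.

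The size is uncertain. About 50% of the effect is retained in the extreme case of simple dilution, with 80% power falling to about 29%. Trigger-based scenarios retain roughly 55–90% on the log scale. These figures rest on assumed slopes, variances and post-switch effects, none of which the article gives, so strong dilution is possible but not established. The primary efficacy endpoint is unaffected. This should be corrected, but it does not threaten the trial's main conclusion.

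**What to change.** 1. Keep the as-randomised 3-year ANCOVA, and label and interpret it as early versus deferred ramipril.
2. Add a prespecified supplementary estimate of ramipril versus placebo from a repeated-measures mixed model on the 6-monthly log albuminuria values. Use all values up to and including the progression-defining sample, exclude values after ramipril is started at progression, and report the treatment contrast at 3 years.
3. Do not simply drop switchers. They are selected on high albuminuria, so leaving them out would itself bias the comparison.

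The cost is analysis wording only: efficacy assessments are already 6-monthly, and no visit or treatment rule changes. The downside is that the supplementary estimate relies on missing-at-random and on model-based extrapolation of the untreated course of switchers, with some loss of precision in 80 patients. Missing-at-random is plausible because observed albuminuria triggers the switch, and the retained ANCOVA does not depend on it.

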### 2.8. Ethics Basics, Legislation and Guidelines, and Notification of the Authorities

The Ethics Committee approval concerning the suitability of the trial site and the qualifications of the investigators and conducting the trial was made by the leading Ethics Committee of the University Medical Center Göttingen, Germany (application number Az 11/6/11) in consulting all other participating German Ethics Committees. The clinical trial was also approved by the German competent authority, the Federal Institute for Drugs and Medical Devices (BfArM). Before starting the clinical trial, the state authorities in each federal state of Germany in which the clinical trial will be conducted must be notified.

The study is in adherence with the Declaration of Helsinki. This clinical trial will be conducted in accordance with the published principles of the guidelines for Good Clinical Practice (ICH-GCP) and applicable legislation (the German Medicines Act (AMG) and the GCP-V). All trial subjects enrolled are insured in accordance with § 40 German Medicines Act (AMG).

### 2.9. Data Quality Assurance and Dissemination

Each of the trial sites will be monitored to ensure the quality of the data collected. Monitoring on site will be performed in accordance with the trial-specific standard operating procedures (SOPs), the investigational plan, the guidelines for Good Clinical Practice (ICH-GCP), and local legislation (especially the German Medicines Act (AMG) and the GCP-V). An adapted monitoring concept will be used in accordance to a trial-specific risk assessment. Results will be published irrespective of outcome; written consent will be obtained from the patients/parents/legal guardian.

## 3. Discussion and Conclusion

ACE-inhibitor therapy in AS patients with proteinuria reflects the common off-label treatment [7]. However, long-term therapy with ACEIs in children may lead to long-term drug toxicities unknown in adults. This makes long-term off-label therapy an ethical distress for the pediatric nephrologist. Indications for initiation of treatment by pediatric nephrologists include hematuria alone (3%), microalbuminuria (27%), and overt proteinuria (70%) [4]. Children with AS and proteinuria are thus being treated in a way that prevents the objective assessment of the risks and benefits of therapy. A placebo-controlled clinical trial in children who have not yet developed overt proteinuria is therefore believed not to conflict with the current treatment practices of most pediatric nephrologists [4].

The primary aim of the EARLY PRO-TECT Alport trial is to assess drug safety and efficacy of ramipril treatment in oligosymptomatic pediatric AS patients in the setting of a prospective, placebo-controlled, GCP-conform clinical trial. An integrated translational program will help to define markers of renal disease progression that indicate risk, prognosis, disease activity, and response to therapy without the need for blood sampling or renal biopsy. The results are expected to be of relevance for almost all glomerular renal diseases. Finally, to maximize the available evidence, we will combine the treatment effect estimates from the randomized comparison and Alport registry data. This multimodal concept may serve as a model for other rare pediatric renal diseases, for which trials are similarly difficult to perform.

## Figures and Tables

**Figure 1 fig1:**
[figure not shown]
Study design of the EARLY PRO-TECT Alport trial.

**Figure 2 fig2:**
[figure not shown]
Study visits for the individual patient during the EARLY PRO-TECT Alport.

**Table 1 tab1:** Alport syndrome levels describing renal damage and loss of function.

Stage	Definition
0	Microhaematuria without microalbuminuria (usually at birth)
I	Microalbuminuria (30–300 mg albumin/gCrea)
II	Proteinuria >300 mg albumin/gCrea
III	>25% decline of normal renal function (creatinine clearance)
IV	End-stage renal failure (ESRF)

**Table 2 tab2:** Alport syndrome disease progression in this trial.

Progression	Definition
Stage 0 to I	Albuminuria >30 mg albumin/gCrea in combination with a 3-fold increase from baseline in albuminuria, confirmed within 2 weeks.
Stage I to II	(i) Twofold increase from baseline albuminuria, confirmed within 2 weeks
	(ii) Albuminuria >300 mg albumin/gCrea at a single assessment.

**Table 3 tab3:** Patient eligibility criteria.

	*Inclusion criteria*
	(i) Males or females of any ethnic origin aged between 24 months and <18 years at screening. Female patients of child-bearing potential test negative for pregnancy test and agree to use a reliable method of birth control during the study.
	(ii) Definitive diagnosis of Alport syndrome by kidney biopsy (in patient or other affected family members) and/or genetic testing (hemizygous males with X chromosomal Alport syndrome or homozygous males or females with autosomal recessive Alport syndrome) including screening for clinical diagnostic criteria (hematuria, family history of kidney disease, hearing loss, ocular changes).
	(iii) Alport syndrome stages 0 or I.
	(iv) Previously untreated with ACEIs (patients taking an ACEI for the treatment of Alport syndrome may be included in the open-label treatment arm).
	(v) Written informed consent.

	*Exclusion criteria*
	(i) Uncertain diagnosis or variants of Alport syndrome such as heterozygous carriers.
	(ii) Alport syndrome stages II, III, or IV.
	(iii) Known allergies or intolerances to ramipril or related compounds.
	(iv) Known contraindication for ACEI therapy (e.g., bilateral renal artery stenosis, prior history of angioedema, previous hyperkalemia, or previous acute prerenal renal failure).
	(v) Females with a positive pregnancy test or females who are lactating.
	(vi) Additional other chronic renal, liver, or cardiac diseases.
	(vii) No written informed consent.
